### Interim analyses and stopping guidelines

There will be no interim analysis for the primary trial outcomes. We will analyse baseline process evaluation data from clinician questionnaires after the intervention has been delivered. This will include descriptive statistics, psychometric properties of measures, and exploration of the association between process variables as a preliminary test of the theorised process models. This will be conducted by the study statistician without knowledge of group allocation.

The intervention aims to promote optimal performance of clinical behaviours that are recommended in policy documents and clinical practice guidelines and thus represents a very low risk. Therefore, we have no explicit stopping rules.

### Randomisation: sequence generation

The unit of randomisation will be the general practice: Randomisation will be performed by a statistician independent of the study team, using computer-generated random permuted blocks and will be stratified by practice size (the only organisation characteristic found to be related to performance in our previous study, iQuaD).

Random sample of 100 patients within clusters: The study statistician will provide each practice with a computer-generated list of random numbers to use for selecting which patients with type 2 diabetes to send a survey from their practice diabetes register.

### Randomisation: type

Permuted-block randomisation, with practice list size as the blocking factor; 22 practices will be randomised to intervention, and 22 to control. The size of the permuted blocks will vary randomly.

### Randomisation: allocation concealment mechanism

Each practice will eventually become aware of their allocation but allocation will be concealed from them until baseline process evaluation questionnaires have been returned to the research team. Within a practice, patients are not being allocated to alternative treatments so allocation concealment is not an issue.

### Randomisation: implementation

Clusters: NHS North of England Commissioning Support Unit will be involved in inviting all clusters to participate prior to randomisation. The study RA will send the study statistician anonymised practice ID codes and associated patient list sizes. The study statistician will generate the random sequence and allocate practices to two separate dummy-coded groups without knowledge of which group will receive the intervention; the study statistician will remain blind to allocation until follow-up data has been collected. Random allocation of clusters to intervention or control will take place consecutively as practices are recruited and until our target sample size (44) is reached.

Patients: The study statistician will generate the random sequence but will not be involved in the implementation of the randomisation. The statistician will provide each random number list to the study RA, who will send a random number list to the practice contact at each of the 44 practices to be used to select a random sample of 100 patients per practice to be sent questionnaires.

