### Recruitment

#### Step one: general practice recruitment

Potential participating clusters (*i.e.*, general practices) will be invited to participate by research facilitators who will identify a practice contact as a primary point of contact for the research team. The study research associate (RA) will also present the study design at local GP research forums to garner interest. Once identified, the study RA will contact practices to obtain written practice-level agreement to participate in the trial in principle and to subsequently arrange details of attendance of GPs, nurses and healthcare assistants at the intervention delivery sessions.

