#### Step two: clinician recruitment

Once practices are recruited, the study RA will contact practices to conduct a telephone interview to identify practice structure features and all clinicians in the practice providing care to people with Type 2 diabetes who may be interested in participating. Each identified clinician will be provided with a study invitation pack by post via the practice contact, including a letter of invitation, information sheet, consent form and baseline questionnaire.

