### Blinding

Given the nature of the intervention, GPs, nurses and healthcare assistants will inevitably be aware of their allocation and thus blinding of participants will not be possible. Each practice contact will become aware of allocation. To minimise recruitment bias, random allocation to intervention and control will take place after practices are recruited but practices will not be informed of allocation until after both practices and individual clinicians are identified and recruited (*i.e.*, not until after baseline clinician questionnaires are returned completed). Patients within each practice will remain blind to allocation. The outcome assessor for data from the practice computers will be kept blind to the allocation. The practice contact that will use the random sequence of numbers to identify the random sample of 100 patients within each practice invited to complete the patient survey will possibly not be blind to allocation. Blinding of the full research team is also not possible as intervention practices will be contacted to arrange the intervention sessions. However, the study statistician conducting the outcome analysis will remain blinded to allocation until after the outcome data have been collected at follow-up.

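### Practices are allocated before their clinicians are enrolled, and concealment covers the practices but not the research associate who enrols those clinicians

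*Protocol article*

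**What the plan says.** The order of events is spread over five sections of the protocol article.

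- *Step one: general practice recruitment.* The study RA obtains written practice agreement and is later to "arrange details of attendance of GPs, nurses and healthcare assistants at the intervention delivery sessions".
- *Step two: clinician recruitment.* This stage begins only when the practice has joined: "Once practices are recruited, the study RA will contact practices to conduct a telephone interview". Clinicians identified in that call receive a postal pack through the practice contact. It holds the invitation, information sheet, consent form and baseline questionnaire.
- *Randomisation: implementation.* "Random allocation of clusters to intervention or control will take place consecutively as practices are recruited". Allocation stops at 44 practices. The RA sends practice codes and list sizes to the study statistician, who allocates to two dummy-coded groups without knowing which is which. The section does not say who receives the codes or who can decode them.
- *Randomisation: allocation concealment mechanism.* Of the practices it says that "allocation will be concealed from them until baseline process evaluation questionnaires have been returned to the research team".
- *Blinding.* "To minimise recruitment bias, random allocation to intervention and control will take place after practices are recruited", with the result withheld from practices until their clinicians are enrolled and baseline questionnaires are back. The same section adds: "Blinding of the full research team is also not possible as intervention practices will be contacted to arrange the intervention sessions".

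**The concern.** In a cluster trial where individuals are enrolled after the cluster is allocated, the person enrolling them should not know the arm. Here clinician enrolment can follow allocation, and the written concealment is directed at the practice only. The RA both enrols clinicians and arranges sessions, and arranging sessions is the one activity the protocol names as breaking the blind.

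An RA who knew the arm could, without intending to, list or follow up clinicians differently in the two arms. That would affect:

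- the comparison of theoretical constructs and the mediation models;
- the clinician survey, which Table 2 lists as a secondary source for all six outcomes;
- the mix of clinicians who receive the intervention.

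A second consequence needs no bias at all. A practice that withdraws during the baseline step has already been randomised. Under intention to treat it counts as a missing cluster, when it could have been replaced before allocation.

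**Working it through.** **Order of steps.** The sections, set side by side, give this sequence:

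1. The practice agrees (*Step one*).
2. The practice is allocated, consecutively with recruitment (*Randomisation: implementation*).
3. Starting from the same point, the RA identifies clinicians by telephone, and packs go out (*Step two*). Non-respondents get two reminders (*Process measures*).
4. Baseline questionnaires come back, and only then is the practice told its arm (*allocation concealment mechanism*; *Blinding*).

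No section makes step 2 wait for step 3. The *Blinding* section contrasts the moment of allocation with the later moment of disclosure. That contrast has a purpose only if the arm exists in the interval.

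**Who is covered by concealment.** Practices, and through them the practice contact and clinicians, are covered until baseline return. The statistician is covered until follow-up data are in. The RA is covered by no statement.

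**How the RA could learn an arm early.** For a single practice, session booking must follow disclosure, so booking does not reveal that practice's arm during its own enrolment. Across practices it is different. There are two fixed dummy groups and allocation is consecutive, so booking the first intervention practice could show which code means intervention while later practices are still enrolling clinicians. This requires that the RA sees the later practices' codes. The protocol neither says so nor rules it out. *Randomisation: sequence generation* gives randomisation to a statistician independent of the study team, whereas *Randomisation: implementation* gives it to the study statistician, so the code holder cannot be worked out from the text.

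**What the primary analysis uses.** Prescribing and foot examination use the records of all type 2 patients in the practice. Advice uses a random sample of 100 patients per practice (*Sample size*). The comparison is by practice as randomised (*Main trial analysis*). Clinician enrolment enters none of these denominators.

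**Size of the missing-cluster consequence.** Inputs from *Sample size*: 42.5% v 57.5%, ICC 0.06, 20 patients per practice, 5% significance (two-sided assumed).

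- Design effect: 1 + (20 − 1) × 0.06 = 2.14.
- Patients per arm, continuity-corrected and before clustering: 187. Practices per arm: 187 × 2.14 / 20 = 20.01, or 40 in total, as stated.
- Spare practices: 44 − 40 = 4, which is 4/44 = 9.1%.
- Effective n per arm: 22 × 20 / 2.14 = 205.6 with 44 practices, and 20 × 20 / 2.14 = 186.9 with 40.
- Power = Φ[(0.15 − 1/n) / √(2 × 0.425 × 0.575 / n) − 1.96], with n the effective n.

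| Practices | Patients per practice | Stated power | Recomputed |
|---|---|---|---|
| 44 | 20 | 83.9% | 84.5% |
| 40 | 20 | 80% | 80.8% |
| 44 | 40 | 92% | 92.4% |
| 40 | 40 | 89% | 89.8% |

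The last two rows use a design effect of 1 + 39 × 0.06 = 3.34. If all four spares were lost evenly across arms, power would fall by 83.9 − 80 = 3.9 points at 20 patients per practice (recomputed 3.7), or by 92 − 89 = 3 points at 40 (recomputed 2.6). The protocol gives no rate of withdrawal at the baseline step, so the number lost there cannot be predicted.

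**The case against.** The best defence is that the protocol never says the RA knows a practice's arm while enrolling its clinicians. The only stated cause of unblinding is session booking, which comes after that practice's baseline return. Packs go by post through a contact who has not yet been told, the RA asks for all clinicians providing this care, and reminders are planned for both baseline and follow-up. A journal article may also leave the code holder to the full protocol. All of this stands, so RA foreknowledge is a possibility the text leaves open and not a stated fact. The order of allocation and enrolment is different: the article fixes it, so it is more than an omitted detail.

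A reader might infer that the protection against recruitment bias fails altogether. The text does not support that. Practices, contacts and clinicians remain unaware until baseline return, so self-selection by arm is prevented as written.

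A reader might also take the disclosure rule to require a questionnaire from every invited clinician, so that many practices could never be told their arm. The wording does not require this. It explains what counts as recruited clinicians, consent form and questionnaire travel in one pack, and non-respondents are expected. What remains is that no closing date is given for the baseline step.

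On missing clusters, the protocol already allows four extra practices and plans sensitivity analyses. A practice that withdraws before disclosure also does so unaware of its arm, so the expected harm is mainly lost precision.

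**Conclusion.** The point holds in a limited form. Allocation is written to occur before clinicians are enrolled, and concealment during enrolment does not extend to the person enrolling them. The exposure is to the clinician sample: process evaluation, clinician-survey secondary data and who receives the intervention. It is not to the primary-outcome denominators, and the planned sample size is unchanged. The size of any bias cannot be calculated from the document, because it depends on whether the RA sees later practices' codes and acts differently as a result.

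The separate cost is that withdrawals at the baseline step become missing clusters. That cost is bounded at about 3 to 4 points of power if all four spares go this way. The bound assumes even loss between arms and no replacement of randomised practices; the protocol describes no replacement and stops allocating at 44. The change is worth making because it is cheap and removes both problems, although neither is shown to have occurred.

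**What to change.** Amend *Randomisation: allocation concealment mechanism*, *Randomisation: implementation* and *Blinding* so that each practice follows one order:

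1. Written practice agreement.
2. Telephone interview, after which the clinician list is fixed.
3. Packs and both reminders, with the baseline survey closing a set time after the second reminder, whatever the response.
4. Only then are the practice code and list size sent for allocation, and the arm disclosed.

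Practices that drop out before step 4 are replaced and do not count towards the 44. While these sections are open, state which statistician allocates and who holds the group key.

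Consecutive allocation in stratified, randomly varying blocks can continue. The cost is that allocation and session booking for each practice move later by the length of its baseline period. No extra patients or staff are needed. Stating only that the RA is kept unaware until baseline return would close the foreknowledge gap, but practices withdrawing at baseline would still be randomised losses.

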### Blinding

Given the nature of the intervention, GPs, nurses and healthcare assistants will inevitably be aware of their allocation and thus blinding of participants will not be possible. Each practice contact will become aware of allocation. To minimise recruitment bias, random allocation to intervention and control will take place after practices are recruited but practices will not be informed of allocation until after both practices and individual clinicians are identified and recruited (*i.e.*, not until after baseline clinician questionnaires are returned completed). Patients within each practice will remain blind to allocation. The outcome assessor for data from the practice computers will be kept blind to the allocation. The practice contact that will use the random sequence of numbers to identify the random sample of 100 patients within each practice invited to complete the patient survey will possibly not be blind to allocation. Blinding of the full research team is also not possible as intervention practices will be contacted to arrange the intervention sessions. However, the study statistician conducting the outcome analysis will remain blinded to allocation until after the outcome data have been collected at follow-up.

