### Exclusion criteria

Practice-level: practices included in pilot study. Clinician level: clinicians who work across multiple different general practices (*e.g.*, district nurses; to avoid contamination). Patient level exclusions: patients with type 1 diabetes or those for whom the primary care team consider it would be clinically inappropriate (*e.g.*, complex comorbidity, frailty, major psychiatric problems).

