#### Step three: patient recruitment

From our previous study [9], we identified that advising behaviours are not consistently recorded in patient notes. We therefore conducted a patient survey to ask patients to report on whether they had received this care in the past year. Consistent with this approach, we will invite a random sample of 100 patients with type 2 diabetes from each practice to complete an anonymous postal questionnaire 12 months after the delivery of the intervention. Patients with type 2 diabetes will be randomly selected from practice lists by the study contact in each recruited practice using a random sequence provided by the study statistician. Patients will be anonymous to the research team.

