### Sample size

Practice-level: 44 practices. Individual-level: The study is powered to detect change in the primary outcomes (six different clinical behaviours) between intervention and control practices. For advising behaviours, the primary outcome measure will be patients’ reports of having received the specific behaviours. In this respect, a random sample of 100 patients with type 2 diabetes in each practice will be surveyed. For prescribing and examining behaviours, data will be extracted from the patient computer records of all patients with type 2 diabetes in each practice. Based on our previous study an intra-cluster correlation coefficient (ICC) of 0.06 is expected and to detect a 15% absolute improvement in any of our measures of behaviour (conservatively calculated as 42.5% to 57.5%) with 80% power and 5% significance, our primary and conservative sample size estimate is that we will need 20 patients from a total of 40 practices. As this sample size does not account for any potential loss to follow-up, we will recruit a further four practices (44 in total). Accordingly, two groups of 22 practices will provide us with 83.9% power to detect a 15% improvement in any behavioural outcome. Our previous study (iQuaD) has demonstrated that this level of recruitment at the patient level is achievable, as we received postal outcome data from a mean of 41 patients per practice (having invited 100) and extracted prescribing data on all patients with type 2 diabetes in the practice (from analysing these data we identified that about 20 patients per practice were eligible for the specified prescribing behaviours). Based on our previous study we anticipate a mean sample size of 40 patients per practice and will thus have greater power. Assuming 40 practices (two groups of 20), we would have 89% power to detect a difference of 15 percentage points (42.5% versus 57.5%) assuming a type 1 error rate of 5% and an ICC of 0.06; retaining all 44 practices would increase power to 92%.

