### Outcome measures (patient survey)

We will use a short questionnaire to assess patients’ reports of having received care, assessed 12 months after the intervention delivery. The three advising behaviours are not reliably recorded in general practice computer systems [9], and measures of these will be acquired by a self-administered patient survey.

Using an anonymous survey we will ask people with diabetes in the study practices about their experiences of their clinicians providing advice about nutrition, physical activity, general education about their diabetes and foot examination, and their confidence in understanding and enacting of their diabetes care.

Each practice will be provided with 100 patient questionnaires, coded by the research team with their practice study code and a patient code of 1 – 100 (*e.g.* 001/001), and 100 reply paid envelopes. Patients will return their questionnaires directly to the research team. The practice will not be aware of which patients have or have not responded to the questionnaire, giving further protection to patients’ confidentiality.

We will explore the potential of conducting a second mailing to the same random sample of patients a month later to promote a higher response. Patient consent to participate in the anonymised survey will be assumed by the receipt of a completed questionnaire.

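### Three primary outcomes rest on a survey sample drawn and clinically screened inside each practice, and nothing fixes eligibility before the practice learns its arm

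*Protocol article*

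**What the plan says.** **Which outcomes are affected.** Table 2 gives the patient survey as primary data source for three of the six primary outcomes. Outcome measures (patient survey) explains why: "The three advising behaviours are not reliably recorded in general practice computer systems". The Sample size section confirms it: "For advising behaviours, the primary outcome measure will be patients’ reports of having received the specific behaviours".

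**Who selects, and when patients are asked.** Under Step three: patient recruitment, patients are "randomly selected from practice lists by the study contact in each recruited practice using a random sequence provided by the study statistician", and are invited to "complete an anonymous postal questionnaire 12 months after the delivery of the intervention".

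**Who may be left out.** The patient-level Exclusion criteria remove "those for whom the primary care team consider it would be clinically inappropriate", with complex comorbidity, frailty and major psychiatric problems as examples.

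**Who knows the allocation.** Practices are told their arm after the baseline clinician questionnaires are returned. The Blinding section accepts that GPs, nurses and healthcare assistants cannot be blind. Of the practice contact it says first "Each practice contact will become aware of allocation", and later that the person who uses the numbers to "identify the random sample of 100 patients within each practice invited to complete the patient survey will possibly not be blind to allocation".

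**What is said about concealment.** The allocation concealment section states that, within a practice, "patients are not being allocated to alternative treatments so allocation concealment is not an issue".

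**The concern.** In a cluster trial the practice is randomised, but patients are often chosen for measurement afterwards. If staff who know the practice's arm influence which patients are measured, the arms can differ at follow-up for reasons unrelated to the intervention. Randomising practices does not prevent this.

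The Blinding section recognises the risk one level up. To limit recruitment bias, practices and clinicians are identified and recruited before allocation is disclosed. The patient sample gets no equivalent protection. The one discretionary step, exclusion on clinical grounds, belongs to a team whose members know their arm once it is disclosed, and whose advising is the behaviour under test.

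One survey sample feeds three primary outcomes, and the Discussion calls the trial positive if at least two of the six behaviours change. A selection effect would therefore bear on several outcomes together. The secondary sources for these three are clinician self-report and QOF data whose use is only to be explored. Neither would reveal a distorted survey sample.

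**Working it through.** **1. Tracing the selection step**

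| Step | Where stated | Protected from knowledge of arm? |
|---|---|---|
| Practices and clinicians recruited | Blinding | Yes, before disclosure |
| Random numbers generated | Randomisation: sequence generation; implementation | Yes, by the study statistician |
| Numbers applied to the register | Step three; Blinding | Not assured; the practice contact does this |
| Clinical exclusion of patients | Exclusion criteria | Not assured; the primary care team judges, at an undated point |
| Patient answers and returns the form | Blinding; Outcome measures (patient survey) | Yes; patients are blind and reply directly to the research team |

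The two middle steps are open. Patients are anonymous to the research team, so the team cannot check how either was carried out. No count of exclusions by arm is described.

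**2. Reproducing the plan's power figures**

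Inputs from Sample size: 42.5% versus 57.5%, ICC 0.06, 5% significance (two-sided assumed). Effective sample size per arm is n = k·m / [1 + (m − 1)·0.06], with k practices per arm and m patients per practice. Power is from the normal approximation with pooled null variance and continuity correction (difference reduced by 1/n).

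| k per arm | m | n | Power | Stated |
|---|---|---|---|---|
| 20 | 20 | 186.9 | 80.1% | 80% |
| 22 | 20 | 205.6 | 84.0% | 83.9% |
| 20 | 40 | 239.5 | 89.4% | 89% |
| 22 | 40 | 263.5 | 92.1% | 92% |

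The plan's figures reproduce, so its own inputs can be used to scale a bias.

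**3. Scale of a selection effect (illustration)**

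The document gives no exclusion rate. Assume intervention practices exclude an extra 10% of patients, and that those patients would report advice 20 to 30 points less often than the patients kept. With no true effect, the spurious difference is 0.10 × (20 to 30) = 2 to 3 points.

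The standard error of the arm difference at a 50% rate, with 22 practices per arm and 40 replies each, has design effect 1 + 39 × 0.06 = 3.34:

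SE = √(2 × 0.25 × 3.34 / 880) = 0.0436, or 4.36 points.

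The two-sided false-positive rate for shift d is Φ(−1.96 + d/SE) + Φ(−1.96 − d/SE):

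- d = 2 points: 7.4%
- d = 3 points: 10.6%

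Nutrition advice is limited to BMI above 30, so fewer than 40 replies per practice count. Assuming 20, the design effect is 2.14 and SE = √(2 × 0.25 × 2.14 / 440) = 0.0493. The rates become 6.9% and 9.3%.

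**4. Range under a different assumption**

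Suppose instead that intervention practices additionally exclude a fraction f of the patients who would report no advice. At a 50% rate the shift is 0.5 / [0.5 + 0.5(1 − f)] − 0.5. With 40 replies per practice:

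| f | Shift (points) | False-positive rate |
|---|---|---|
| 5% | 1.3 | 6% |
| 10% | 2.6 | 9% |
| 20% | 5.6 | 25% |
| 30% | 8.8 | 53% |

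The larger values of f show only how the result depends on the assumption. Nothing in the document makes them likely.

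**5. The two-of-six rule**

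The Multiple comparisons section gives 0.033 as the chance of two or more significant results under independence, and this reproduces. Put the step 3 rates on the survey outcomes (two at 40 replies, nutrition advice at 20) and 5% on the other three. The chance becomes 4.8% for a 2-point shift and 6.9% for a 3-point shift. The plan itself treats independence as a rough guide only.

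**The case against.** **Timing.** A reader might infer that patients are chosen and pruned a year after the practice learned its arm. The document does not say so. It dates the questionnaire, but not the draw, the dispatch of the number list or the clinical screen, nor whether screening precedes the draw. Operational detail of that kind may sit in the full protocol. This objection stands, and the point is limited accordingly: the text assigns the discretion to the practice and states nothing that settles it before disclosure.

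**The concealment statement.** A reader might take it as denying a known problem. Read literally, it concerns allocation within a practice and is true. It simply does not reach selection by staff who know the practice's arm. The Blinding section discloses that separately.

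**Safeguards.** Externally generated numbers, blind patients and direct return of forms are real protections. They cover the draw and the reporting, but not the exclusion.

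**Size and direction.** Bias needs the same criterion to be applied differently in the two arms, and the document offers no evidence that it would be. Patients with comorbidity might have more contact and receive more advice, which would reverse the sign and hide a benefit. The illustrated 2 to 3 points are below one standard error and small beside the 15-point target. All of this stands, so the figures are illustration and not an estimate.

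**Fixing the sample early.** Naming the 100 patients before disclosure would tell practices for a year whose reports count, and could invite selective advising. This also stands, and it shapes the fix.

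**Conclusion.** The point holds in limited form. Three primary outcomes depend on a sample that practice staff draw and may screen by clinical judgement, and the document gives no protection against that judgement being made with the arm known. It does not show that bias will occur, in which direction, or how large it would be. Under the stated assumptions (a shift of 2 to 3 points, a 50% rate, 44 practices, ICC 0.06), the false-positive rate for one outcome moves from 5% to about 7-11% with 40 replies per practice, and to about 7-9% for nutrition advice if 20 replies per practice count.

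An analysis plan cannot repair this, because it concerns how the sample is formed. Separately, the two statements in the Blinding section about the practice contact do not agree: one is certain that the contact will learn the allocation, the other only allows that this is possible. The change is worth making because it costs little and removes most of the doubt.

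**What to change.** 1. Have each practice mark clinical exclusions on its whole type 2 diabetes register before allocation is disclosed, when the baseline clinician questionnaires are returned.
2. Do not draw or reveal the 100 patients at that stage. Release the random number list at month 12 and draw from the pre-marked register, so that practices cannot know in advance whose reports will be measured.
3. Allow later exclusions, and screening of newly diagnosed patients, only with a logged reason.
4. Have each practice return register size, exclusions by reason and timing, and number of questionnaires mailed. Report these by arm.
5. In the allocation concealment section, limit the statement to allocation within a practice and say how selection of survey patients is protected.
6. In the Blinding section, reconcile the two descriptions of what the practice contact knows.

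**Cost.** Each practice screens its whole register once, instead of only the patients drawn, and keeps a short log. Some exclusions will still be made after disclosure, but they will be visible by arm. The sample size and the analysis do not change.
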